### 2. Metric Calculation at Each Time Point

Sort samples in descending order of risk scores.

For each time point  $t$ , define:

- **TP** (true positives)
- **FP** (false positives)
- **TN** (true negatives)
- **FN** (false negatives)

In the computation of these quantities, the IPCW is applied to the counts of events. For instance, the true positive count is computed as the sum of IPCW-adjusted indicators for cases (i.e., if an event occurs before or at time  $t$ ).

Compute performance metrics including:

- **AUC:**  $AUC_t = \int_0^1 TPR_t(FPR_t) dFPR_t$  where  $TPR_t$  is the true positive rate (sensitivity) and  $FPR_t$  is the false positive rate (1 - specificity) at time  $t$
- **Sensitivity:**  $Sensitivity_t = \frac{TP_t}{TP_t + FN_t}$
- **Specificity:**  $Specificity_t = \frac{TN_t}{TN_t + FP_t}$
- **F1 Score:**  $F1_t = \frac{2 \cdot Precision_t \cdot Recall_t}{Precision_t + Recall_t}$
- **Precision:**  $Precision_t = \frac{TP_t}{TP_t + FP_t}$
- **Accuracy:**  $Accuracy_t = \frac{TP_t + TN_t}{TP_t + FP_t + TN_t + FN_t}$
- **Recall:**  $Recall_t = \frac{TP_t}{TP_t + FN_t}$
- **Matthews Correlation Coefficient (MCC):**

$$MCC_t = \frac{((TP_t * TN_t) - (FP_t * FN_t))}{\sqrt{(TP_t + FP_t) * (TP_t + FN_t) * (TN_t + FP_t) * (TN_t + FN_t)}}$$

- **Positive Predictive Value (PPV) and Negative Predictive Value (NPV):**

$$PPV_t = \frac{TP_t}{TP_t + FP_t} \text{ and } NPV_t = \frac{TN_t}{TN_t + FN_t}$$

The binary classification threshold at each time point is chosen to maximize the sum of sensitivity and specificity.

### 3. **Weighted Aggregation (for Multiple Time Points)**

If multiple time points are evaluated, compute the weighted mean of each metric using the survival probability at each time point

$$\bar{M} = \frac{\sum_{t=1}^m M_t \cdot \hat{S}(t)}{\sum_{t=1}^m \hat{S}(t)}$$

where  $M_t$  is the metric at time  $t$  and  $\hat{S}(t)$  is the estimated survival probability.

The function returns a dictionary containing the performance metrics at each time point, along with the overall weighted mean metrics if applicable. The pseudo code is as follows:

```

import numpy as np
from sksurv.util import check_y_survival
from sksurv.nonparametric import CensoringDistributionEstimator, SurvivalFunctionEstimator
def cum_metrics(survival_train, survival_test, estimate, times, AUC_sfd=False,
                tied_tol=1e-8):
    test_event, test_time = check_y_survival(survival_test)
    event_shuffle = test_event
    estimate, times = _check_estimate_2d(estimate, test_time, times,
                                         estimator="cumulative_dynamic_auc")

    n_samples = estimate.shape[0]
    n_times = times.shape[0]
    if estimate.ndim == 1:
        estimate = np.broadcast_to(estimate[:, np.newaxis], (n_samples, n_times))
    cens = CensoringDistributionEstimator()
    cens.fit(survival_train)
    ipcw = cens.predict_ipcw(survival_test)
    test_time = np.broadcast_to(test_time[:, np.newaxis], (n_samples, n_times))
    test_event = np.broadcast_to(test_event[:, np.newaxis], (n_samples, n_times))
    times_2d = np.broadcast_to(times, (n_samples, n_times))
    ipcw = np.broadcast_to(ipcw[:, np.newaxis], (n_samples, n_times))
    o = np.argsort(-estimate, axis=0)
    test_time = np.take_along_axis(test_time, o, axis=0)
    test_event = np.take_along_axis(test_event, o, axis=0)
    estimate = np.take_along_axis(estimate, o, axis=0)
    ipcw = np.take_along_axis(ipcw, o, axis=0)
    is_case = (test_time <= times_2d) & test_event
    is_control = test_time > times_2d
    n_controls = is_control.sum(axis=0)
    estimate_diff = np.concatenate((np.broadcast_to(np.infty, (1, n_times)),
                                   estimate))

    is_tied = np.absolute(np.diff(estimate_diff, axis=0)) <= tied_tol
    CU_tp = np.cumsum(is_case * ipcw, axis=0)
    CU_fp = np.cumsum(is_control, axis=0)
    CU_tn = n_controls - CU_fp
    CU_fn = CU_tp[-1] - CU_tp
    CU_n_neg = CU_tn + CU_fn
    CU_n_pos = CU_tp + CU_fp
    tpr_all = CU_tp / CU_tp[-1] # sensitivity
    fpr_all = CU_fp / (CU_tn + CU_fp) # 1 - specificity
    pr_all = CU_tp / (CU_tp + CU_fp + 1)
    tnr_all = 1 - pr_all
    ac_all = (CU_tp + CU_tn) / (CU_tn + CU_fn + CU_tp + CU_fp)
    fnr_all = CU_fn / (CU_tp + CU_fn)
    mmc_all = ((CU_tn * CU_tp) - (CU_fp * CU_fn)) / \
        np.sqrt((CU_tn + CU_fn) * (CU_fp + CU_tp) * (CU_tn + CU_fp) * (CU_fn + CU_tp))
    prev_all = (CU_tp + CU_fn) / (CU_tn + CU_fn + CU_tp + CU_fp)
    ppv_all = ((tpr_all) * prev_all) / ((tpr_all * prev_all) + ((fpr_all) * (1 - prev_all)))
    npv_all = ((1 - fpr_all) * (1 - prev_all)) / (((1 - tpr_all) * prev_all) + \
        ((1 - fpr_all) * (1 - prev_all)))
    res_keys = ["AUC", "AUC_P", "best_spe", "best_sen", "f1_scores", "best_pr",

```

```

        "best_rec", "best_ac", "best_fpr", "best_fnr", "best_mcc", "best_ppv",
        "best_npv"]
res = {key: np.empty(n_times, dtype=float) for key in res_keys}
it = np.nditer((tpr_all, fpr_all, pr_all, ac_all, fpr_all, fnr_all,
                mmc_all, ppv_all, npv_all, CU_n_pos, CU_n_neg, is_tied), order="F",
                flags=["external_loop"])
with it:
    for i, (tpr, fpr, pr, ac, fpr2, fnr, mmc, ppv, npv, n_pos, n_neg, mask) in enumerate(it):
        idx = np.flatnonzero(mask) - 1
        tpr_no_ties = np.r_[0, np.delete(tpr, idx)]
        fpr_no_ties = np.r_[0, np.delete(fpr, idx)]
        pr_no_ties = np.r_[0, np.delete(pr, idx)]
        res['AUC'][i] = np.trapz(tpr_no_ties, fpr_no_ties)
        if type(AUC_sfd) != bool:
            res['AUC_P'][i] = (np.sum(AUC_sfd[:, i] >= res['AUC'][i]) + 1) / \
                (len(AUC_sfd[:, i]) + 1)
        best_index = np.argmax(tpr_no_ties + (1 - fpr_no_ties))
        res['best_sen'][i] = tpr_no_ties[best_index]
        res['best_spe'][i] = 1 - fpr_no_ties[best_index]
        res['best_ac'][i] = np.r_[0, np.delete(ac, idx)][best_index]
        res['best_fpr'][i] = fpr_no_ties[best_index]
        res['best_fnr'][i] = np.r_[0, np.delete(fnr, idx)][best_index]
        res['best_mcc'][i] = np.r_[0, np.delete(mmc, idx)][best_index]
        res['best_ppv'][i] = np.r_[0, np.delete(ppv, idx)][best_index]
        res['best_npv'][i] = np.r_[0, np.delete(npv, idx)][best_index]
        f1 = 2 * (pr_no_ties * tpr_no_ties) / (pr_no_ties + tpr_no_ties + \
            np.finfo(float).eps)
        res['best_pr'][i] = pr_no_ties[np.argmax(f1)]
        res['best_rec'][i] = tpr_no_ties[np.argmax(f1)]
        res['f1_scores'][i] = f1[np.argmax(f1)]
    if n_times == 1:
        return res, []
    else:
        surv = SurvivalFunctionEstimator()
        surv.fit(survival_test)
        s_times = surv.predict_proba(times)
        d = -np.diff(np.r_[1.0, s_times])
        res_mean = {key: (res[key] * d).sum() / (1.0 - s_times[-1]) for key in res_keys}
    return res, res_mean

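### The SAP's evaluation code weights cases but not controls for censoring, and picks each cut-off on the data it evaluates, so PPV is overstated and NPV is misstated by horizon

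*Combined protocol and SAP*

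**What the plan says.** SAP section 7, step 1, defines a censoring weight for every person at each time, conditional on covariates. Step 2 narrows its use: "In the computation of these quantities, the IPCW is applied to the counts of events". The code follows step 2. Cases are weighted ("CU_tp = np.cumsum(is_case * ipcw, axis=0"). Controls are everyone still observed after the time point ("is_control = test_time > times_2d") and are counted raw ("CU_fp = np.cumsum(is_control, axis=0"). The two kinds of count are then added: "prev_all = (CU_tp + CU_fn) / (CU_tn + CU_fn + CU_tp + CU_fp". PPV and NPV are built from that prevalence; accuracy, precision, F1 and MCC use the same mixed counts.

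On the cut-off, step 2 says: "The binary classification threshold at each time point is chosen to maximize the sum of sensitivity and specificity". The code takes this maximum over the outcomes of the set being evaluated. Training outcomes enter only to fit the censoring curve.

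For several time points, the text of step 3 says to "compute the weighted mean of each metric using the survival probability at each time point". The code instead uses "d = -np.diff(np.r_[1.0, s_times" as weights, that is, the drop in survival between successive times.

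**The concern.** Weighted cases stand for the whole cohort. Raw controls stand only for the part of it not yet censored. Adding them makes events look more common than they are, increasingly so as follow-up thins. PPV and NPV inherit this error. It also depends on each cohort's censoring pattern, so these metrics would not be comparable across PMBB, ARIC and UK Biobank.

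Separately, a cut-off tuned on the outcomes it is then scored on gives best-case values. The test set holds only 32 composite events in 171 people (Supplementary Table 1). The stated aim is to identify and target people early, so a reader will look at predictive values as well as at discrimination.

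**Working it through.** **No figure to reproduce.** The documents state no PPV, NPV, sensitivity or specificity. The event proportion reproduces: 32/171 = 18.71%.

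**Algebra (independent censoring).** For N people:
- weighted cases by t estimate N×F
- raw controls estimate N×S×G
- coded prevalence = F/(F + S×G), which exceeds F whenever G < 1
- the false-positive rate is a ratio of two control counts, so a common factor 1/G(t) cancels; sensitivity uses cases only. AUC, sensitivity and specificity do not move.

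Illustration with F = 0.187 and sensitivity = specificity = 0.75. For G = 0.8, coded prevalence is 0.187/(0.187 + 0.813×0.8) = 0.223, and PPV is 0.75×0.223/(0.75×0.223 + 0.25×0.777) = 0.463.

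| G(t) | Coded prevalence | PPV | NPV |
|---|---|---|---|
| 1 (correct) | 0.187 | 0.408 | 0.929 |
| 0.9 | 0.204 | 0.434 | 0.921 |
| 0.8 | 0.223 | 0.463 | 0.913 |
| 0.6 | 0.277 | 0.535 | 0.887 |
| 0.4 | 0.365 | 0.633 | 0.839 |

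**Assumed G(t).** Supplementary Table 1 gives test-set follow-up of 7.43 ± 2.78 years; Protocol 3.6 caps follow-up at 10 years. I treated follow-up time as censoring time, with a Beta shape on 0 to 10 years: 0.743×0.257/0.278² − 1 = 1.471, so the parameters are 0.743×1.471 = 1.093 and 0.257×1.471 = 0.378. This gives G(5) = 0.79, G(8) = 0.57 and G(9) = 0.44.

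**Simulation of the coded rule.** 1,500 replicates, 680 training and 171 test, hazard set to give 18.7% observed events, true AUC about 0.81. Fixed means controls weighted by 1/G(t) at the same cut-off. True is the population value at that cut-off.

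| Year | Prevalence coded / fixed / true | PPV coded / fixed / true | NPV coded / fixed / true | Sens + spec coded / true |
|---|---|---|---|---|
| 5 | 0.170 / 0.140 / 0.140 | 0.418 / 0.365 / 0.325 | 0.946 / 0.957 / 0.939 | 1.533 / 1.432 |
| 8 | 0.312 / 0.205 / 0.202 | 0.613 / 0.479 / 0.430 | 0.883 / 0.930 / 0.909 | 1.530 / 1.439 |
| 9 | 0.395 / 0.223 / 0.220 | 0.703 / 0.520 / 0.458 | 0.843 / 0.923 / 0.900 | 1.542 / 1.441 |

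- Weighting fault alone, PPV: 0.418 − 0.365 = 0.053; 0.613 − 0.479 = 0.134; 0.703 − 0.520 = 0.183.
- Both faults together, NPV: 0.946 − 0.939 = +0.007; 0.883 − 0.909 = −0.026; 0.843 − 0.900 = −0.057.
- Sensitivity plus specificity: overstated by 0.09 to 0.10 against the truth at the same cut-off, and by 0.08 to 0.09 against a cut-off fixed in training (1.446, 1.452, 1.453).
- With AUC about 0.73 the pattern holds: PPV excess from weighting 0.049, 0.135 and 0.194; net NPV error +0.007, −0.032 and −0.072.

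**Other mismatches between text and code.**
- Step 2 gives precision and PPV one formula, and recall and sensitivity one formula. The code adds 1 to the precision denominator and takes precision, recall and F1 at a separate F1-maximising threshold. At the same cut-off the added 1 alone lowers precision by 0.011 at 5 years (0.418 to 0.407) and 0.018 at 9 years (0.703 to 0.685).
- Step 1's weight is conditional on covariates; the code's censoring curve uses none.
- The two time-averages agree for evenly spaced times under a roughly constant hazard, but not otherwise. Take times 1, 3, 5 and 9 years (assumed) and a hazard of 32/(171×6.72) = 0.0278 per year. S(t) is then 0.973, 0.920, 0.870 and 0.778. The 9-year value gets weight 0.778/3.541 = 22% by the text and (0.870 − 0.778)/(1 − 0.778) = 41% by the code.
- Follow-up is capped at 10 years, so at t = 10 the coded control set is empty.

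**The case against.** The best counter-argument is that the headline results do not depend on this. Protocol 3.7 names time-dependent AUC and Harrell's C for discrimination. AUC survives the weighting fault, and neither measure uses a cut-off. NNT (SAP 6.5) uses observed event rates at percentile thresholds, not this function's PPV. The coded prevalence is an intermediate that the function never returns. All of this stands, and it limits the severity.

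The Youden-type cut-off is also stated openly. That is true, but openness does not remove the optimism, and section 7 plans no correction for it.

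Four stronger readings are tempting and not supported:
- **NPV is always understated.** That holds for the weighting fault at a fixed cut-off. Cut-off optimism works the other way, and at 5 years the net error is slightly positive.
- **The PPV gap is larger than given here.** Whole-cohort follow-up (Appendix 1, 7.18 ± 2.89 years) gives lower G(t) and bigger gaps, but the figures here concern the test set, where follow-up is longer.
- **The cut-off optimism can be sized with 32 cases and 139 controls.** The code drops people censored before t, so that split describes no horizon with earlier censoring.
- **These cut-offs will be applied to patients.** The function returns metrics, not thresholds, and no section carries a cut-off forward.

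**Conclusion.** The rule is wrong as written in both text and code. The direction of the weighting fault needs only independent censoring before t: at a given cut-off, PPV is too high and NPV too low. Cut-off selection adds about 0.09 to sensitivity plus specificity in a test set of 171.

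The sizes (PPV about 5, 13 and 18 points too high at 5, 8 and 9 years from weighting alone; NPV about right at 5 years and about 3 to 6 points low at 8 to 9) rest on an assumed Beta censoring shape and an AUC of about 0.8. The documents give neither G(t) nor the evaluation times, and 8 and 9 years are my illustrations. A reader should not infer that the discrimination claims or the NNT are inflated by this. Severity: should-fix, because the affected metrics are secondary.

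**What to change.** 1. Weight controls by 1/G(t) in both `CU_fp` and `n_controls`, amend the step 2 sentence to match, and recompute PPV, NPV, accuracy, precision, F1 and MCC.
2. Remove the added 1 in `pr_all`, and report precision, recall and F1 at the same cut-off as the other metrics, so that they match the step 2 formulas.
3. Fix the cut-off for each horizon in the training set and apply it unchanged to the test set, ARIC and UK Biobank.
4. Reconcile text and code on the time-average (S(t) weights or decrements of S) and on the censoring weight (covariate-conditional or marginal). If the conditional weight is chosen, control weights differ between people and no longer cancel, so AUC, sensitivity and specificity need them too.
5. State the evaluation times, all below 10 years, and report estimated G(t) at each.

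The cost is a few lines of code and some SAP wording, with no new data. Reported PPV and the sum of sensitivity and specificity should be expected to look less favourable. Control weighting alone, with the marginal weight, leaves sensitivity and specificity unchanged.

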## 2. Objectives

The primary and secondary objectives are to:

- Develop and validate a plasma APOL1 proteomic risk score (APRS) for prediction of a composite kidney outcome ( $\geq 40\%$  decline in eGFR, initiation of dialysis or kidney transplantation, or all-cause death) in APOL1 high-risk individuals with preserved kidney function.

- Compare APRS performance (discrimination) to standard models including the KFRE, APOL1 genotype status, and CKD polygenic risk scores.

- Externally validate APRS in independent, ancestry-matched cohorts (ARIC and UK Biobank) using harmonized outcomes.

- Assess biological plausibility by evaluating the association of APRS protein components with kidney tissue pathology (e.g., interstitial fibrosis).

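### In the SAP section 7 evaluation code, AUC_P is uninitialised memory by default, and accuracy, NPV and FNR are wrong when the chosen cut classifies nobody as positive

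*Combined protocol and SAP*

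**What the plan says.** SAP section 7 (Model Performance Evaluation), step 2, lists the metrics to be computed at each time: AUC, sensitivity, specificity, F1, precision, accuracy, recall, MCC, PPV and NPV. The classification threshold is the one that maximises sensitivity plus specificity. Step 3 gives the computation as a code listing.

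Four features of the listing matter here.

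- The function is declared as "def cum_metrics(survival_train, survival_test, estimate, times, AUC_sfd=False", so the default is that no null distribution is given.
- All thirteen outputs, `AUC_P` among them, are created by "res = {key: np.empty(n_times, dtype=float) for key in res_keys". `AUC_P` is filled only under "if type(AUC_sfd) != bool", with no alternative branch. A variable whose name suggests a permutation is set by "event_shuffle = test_event" and never used.
- The time average covers every output: "res_mean = {key: (res[key] * d).sum() / (1.0 - s_times[-1]) for key in res_keys".
- The operating point is chosen by "best_index = np.argmax(tpr_no_ties + (1 - fpr_no_ties", from vectors to which a leading 0 has been added. The same leading 0 is added to the other metrics, for example "res['best_fnr'][i] = np.r_[0, np.delete(fnr, idx)][best_index".

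Protocol section 2 sets the objective to "Compare APRS performance (discrimination) to standard models including the KFRE, APOL1 genotype status, and CKD polygenic risk scores". Protocol section 3.5 restricts the primary cohort to carriers of two risk alleles.

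**The concern.** An output that carries a P-value name but holds leftover memory can look like a result. The contents may be absurd, or may lie between 0 and 1 and pass unnoticed.

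The leading 0 is a placeholder that is a correct value for only some of the metrics. Where the threshold rule selects that position, the function reports combinations that cannot occur: sensitivity 0 together with FNR 0, or accuracy 0 although specificity is 1. Accuracy, NPV, PPV and MCC are all planned metrics, and this listing is the plan's only detailed specification of how they are computed. Errors of this kind fall on weak or constant comparators, so wherever such a comparator is tabulated beside APRS they would work in favour of APRS.

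**Working it through.** The documents give no figure for this point, so there is none to reproduce. The check is of what the code does against the definitions in SAP section 7, step 2.

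**1. AUC_P.** With the default argument the condition for writing `AUC_P` is false at every time point, so the array keeps whatever was in memory. The logic was run on simulated data with 680 training and 171 test records (the split in Supplementary Table 1), 34 test events, and times 3, 5, 7 and 9 years.

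- The first call returned values near 6.9e-310.
- A later call returned exactly the previous model's NPVs: 0.961, 0.881, 0.832 and 0.581.
- Six calls with identical data, scores and AUCs gave, at the first time point, 1.00, 0.14, 0.37, 0.88, 0.43 and 0.90.
- With a null of 200 permutations supplied, the entry was a proper value: (0 + 1)/(200 + 1) = 0.005 at every time.

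The P-value formula itself therefore works. The fault is that the entry is returned when the formula has not been run.

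**2. The cut at which nobody is positive.** There TP = 0 and FP = 0, FN is the weighted number of cases and TN the number of controls. Write π(t) = weighted cases / (weighted cases + controls) at time t, which is the prevalence the code uses. Then:

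| Metric | Formula | True value | Code |
|---|---|---|---|
| Sensitivity | TP/(TP+FN) | 0 | 0 |
| Specificity | TN/(TN+FP) | 1 | 1 |
| FNR | FN/(TP+FN) | 1 | 0 |
| Accuracy | (TP+TN)/all | 1 − π(t) | 0 |
| NPV | TN/(TN+FN) | 1 − π(t) | 0 |
| PPV | TP/(TP+FP) | undefined (0/0) | 0 |
| MCC | numerator and denominator both 0 | undefined | 0 |

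**3. When the cut is selected.** For a constant score, removing ties leaves TPR = (0, 1) and FPR = (0, 1). The criterion TPR + (1 − FPR) is then (1, 1). The maximiser returns the first maximum, which is the placeholder. In general the placeholder is selected whenever no real cut gives sensitivity + specificity above 1.

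**4. Size.** For the constant score in the simulated test set:

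| Time (years) | π(t) | True accuracy and NPV | Code |
|---|---|---|---|
| 3 | 0.094 | 0.906 | 0 |
| 5 | 0.186 | 0.814 | 0 |
| 7 | 0.306 | 0.694 | 0 |
| 9 | 0.462 | 0.538 | 0 |

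AUC was 0.5 throughout, which is correct. The π(t) values depend on the simulated event and censoring pattern and are not estimates for PMBB.

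**5. Frequency.** In simulated test sets, about 76 to 80% of uninformative binary markers met the placeholder at one or more of four time points, against about 2% of continuous noise scores. At a single time point, pure-noise continuous scores met it in 0.6 to 0.7% of sets, and continuous scores with AUC about 0.60 in at most 0.03%.

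**The case against.** The strongest reply is that none of this touches a planned result, and much of it stands.

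- `AUC_P` is not among the metrics in SAP section 7, step 2, and no section reports one. A reader might infer that P-values already reported are wrong; the documents do not show that any exist.
- The listing is labelled pseudo code, and its only call uses 30 training and 20 test records of random numbers. As printed it would not reach the faulty lines: a helper function is not imported, and the time grid of 1 to 20 lies outside the seeded test follow-up of 1.48 to 17.86, which the library check rejects. The call is no evidence of what was run on study data.
- A reader might infer that APOL1 genotype is scored as an impossible comparator and that the advantage of APRS is thereby exaggerated. The protocol objective limits that comparison to discrimination, where the returned AUC of 0.5 is right. Genotype is constant only if coded high versus low risk within the all-high-risk set. It varies by diplotype, and in analyses that include the low-risk participants of SAP section 3.
- A reader might take the crude event share of 17.98% (SAP section 3) and put the error at about 0.82 throughout. The code uses a time-specific weighted prevalence, so the error changes with time.

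What does not fall away is that the listing specifies how accuracy, NPV, PPV and MCC are computed, and that it contradicts the definitions in the same section whenever the placeholder is selected. Being called pseudo code does not settle the matter, because no other specification is given.

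**Conclusion.** Two coding errors are confirmed.

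First, `AUC_P` is meaningless unless a null distribution is supplied, yet it is returned and averaged. Any effect on reported results is unproven.

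Second, for a score with no useful cut, FNR is too low by 1, accuracy and NPV are too low by 1 − π(t), and PPV and MCC appear as 0 where they are undefined. This always happens for a constant score, often for an uninformative binary marker, and rarely for continuous scores such as APRS or KFRE.

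AUC, sensitivity and specificity are correct, so the planned comparison of discrimination stands. The documents do not support a claim that APRS has been made to look better. That would require a weak or constant comparator to have been tabulated on accuracy or NPV with this code as printed. The conclusion rests on the working code matching the listing, which the sponsor can confirm.

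**What to change.** - Initialise all outputs with NaN.
- Leave `AUC_P` out of the returned and averaged outputs when no null is supplied, and delete the unused shuffle line. A permutation null needs to be specified only if the sponsor intends to report a P-value for AUC.
- Replace the leading 0 by the true endpoint values: FNR = 1, accuracy = NPV = 1 − π(t), PPV and MCC = NaN. Keep 0 for TPR and FPR.
- Check any existing accuracy, NPV, FNR, PPV, MCC or `AUC_P` output for weak, constant or binary comparators, and rerun what is affected.

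The cost is a few lines of code and a short rerun. No new data are needed.
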